### 2.7. Assignment of Interventions

#### 2.7.1. Allocation

The participants are allocated according to blocked randomization without stratification. A randomized allocation sequence will be assigned to each group based on a computer-generated random number table created by an independent statistician using SAS version 9.4 statistical software (SAS Institute. Inc., Cary, NC, USA). After consent to the clinical trial, the participants’ identification code will be assigned to those who meet the inclusion and exclusion criteria. The participants will be allocated to the WBGCT and control groups at an allocation ratio of 1:1. The randomization table will be retained separately by the independent statistician to maintain blinding. The assignment of participants will be conducted according to the assignment table generated by a random assignment method that can be specifically planned and reproduced in advance. According to the randomized assignment table, the participants’ identification codes will be kept in an opaque envelope and a cabinet with double locks.

#### 2.7.2. Blinding

As this clinical trial is double-blinded, the allocation of participants will be blinded to both the participants and investigators until the clinical trial is completed. The investigators will not be involved in the randomization and do not know what type of drugs the participants will receive. WBGCT and SCRT will be packed in the same wrapping to blind the participants. The identification codes will be developed to prevent the participants from distinguishing their assigned group. Participants will be assigned random numbers and receive medication packages corresponding to the identification code. The investigators will manage the allocation of identification codes, which should not be disclosed until the clinical trial is completed, except in cases of emergency in which the identification code needs to be identified.

### 2.8. Data Management and Monitoring

The investigators should be acquainted with the trial protocol and execute the trial according to the protocol and related regulations. Data will be collected during each visit. The investigator should preserve documents related to the clinical trial during the 3 years after the end of the trial.

Monitoring will be conducted through regular visits and occasional telephone calls by the clinical research associates (CRAs). The CRA will determine whether the clinical trial is being performed in compliance with the protocol, whether AEs are being reported and recorded on case report forms (CRFs), and inspect the consent of the participants and management of investigational medications. The monitors who conduct the monitoring will check the progress of the clinical trials, and problems will be consulted with the investigators.

### 2.9. Statistical Analysis

In this trial, an efficiency analysis will be mainly conducted using a full analysis set (FAS) analysis, and a per-protocol set (PPS) analysis will be performed as needed. The FAS group is defined as the analysis group based on intention-to-treat (ITT) principles. Participants in the FAS group receive the intervention at least once when evaluating efficiency. All data will be included in the analysis after excluding participants who do not meet the exclusion criteria (those who violate the inclusion/exclusion criteria, have never taken investigational medications, or do not provide any data after screening). The PPS analysis group consists of participants who complete the entire trial course with ≥70% compliance to investigational medications without violating the protocol.

Descriptive statistics for each group regarding demographic characteristics and baseline data will be presented. Continuous variables will be expressed as means and confidence intervals, and an independent *t*-test or Wilcoxon rank-sum test will be performed depending on their normality. Categorical variables are expressed as frequencies and percentages, and χ2 test or Fisher’s exact test will be conducted. The primary outcome measures will be analyzed using the mixed effect model repeated measure (MMRM), setting each group and visit as a fixed effect and participants as a random effect. If necessary, the fixed effects will include variables with significant differences in demographic characteristics or variables that can affect chronic cough. Analysis of the primary outcome measures are expressed as mean and 95% confidence interval (CI). Among the secondary outcome measures, CSS scores for 4 weeks against baseline and cough VAS, NDS, LCQ-K, and QCSCS scores will be analyzed using the same methods as the primary outcome measure. Depending on normality, Student’s paired *t*-test or Wilcoxon signed-rank test will be used to analyze differences in scores before and after treatment. The IMOS and IMPSS scores at 2- and 4-week intervals will be analyzed using Fisher’s exact test. Repeated-measures analysis of variance (RM ANOVA) will be used to compare the differences in the changes in CSS score trends between the groups, and Dunnett’s procedure for multiple comparison correction will be used. When performing the Student’s paired *t*-test, Wilcoxon signed-rank test, or RM ANOVA, a missing data will be substituted with Last Observation Carried Forward (LOCF) or Multiple Imputation (MI).

A safety evaluation will be conducted on participants who receive Interventions at least once. The number of AEs between the groups will be compared using Fisher’s exact test. Differences in laboratory test variables before and after treatment will be analyzed using the Student’s paired *t*-test or Wilcoxon signed-rank test.

Economic evaluations will be performed from both social and limited social perspectives. In sensitivity analysis, the available variables will be analyzed using a one-way sensitivity analysis with a tornado diagram. If necessary, a probabilistic sensitivity analysis will be conducted using the distribution and representative values of the variables.

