### 2.2. Participants

#### 2.2.1. Inclusion/Exclusion Criteria

The inclusion criteria are as follows: (1) men and women aged 19–70 years; (2) patients with symptoms of rhinitis or postnasal drip (rhinorrhea, nasal discharge, cough, or nasal itching); or with gross findings of pebble-like appearance in pharyngeal mucosa; or dripping mucus in the throat or with radiological findings of sinusitis in paranasal sinuses (PNS) X-ray; (3) patients with a score above daytime cough symptom score ≥ 2 points and nighttime cough symptom score ≥ 1 point; and (4) patients who voluntarily agreed to participate in this clinical trial in written form.

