
#### 2.2.2. Sample Size

With reference to an exploratory pilot study in which a sample size of 12 per group was recommended [26], the sample size of this trial was 24 participants (12 per group). This is the first randomized controlled trial to investigate the efficacy, safety, and economic evaluation of WBGCT for UACS-induced chronic cough [18]. Considering a 20% dropout rate, 30 participants (15 per group) will be recruited.

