### 2.4. Outcome Measures

#### 2.4.1. Primary Outcome Measures: Cough Symptom Score (CSS)

The CSS is a rating scale for cough frequency during the day and at night. The score for each question ranges from 0 to 5 (with the total score ranging from 0 to 10) [27]. CSS has been used to assess the severity of cough and the efficacy of therapy in many studies on cough [28,29]. In this study, the Korean version of the CSS will be used, which has proven its validity and clinical utility, as well as acceptable repeatability and responsiveness to changes in patients with chronic cough [30]. Participants will evaluate their cough symptoms twice a day using a cough diary (assessment of daytime CCS from 08:00 to 20:00 at 8 PM and assessment of nighttime CSS from 20:00 to 08:00 at 8 AM). CSS will be assessed at visits 1, 2, 3, and 4.

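### The primary MMRM gives a participant random effect as its only dependence term; read literally this forces equal variance and correlation at all visits and can misstate week-2 and week-4 standard errors in either direction

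*Protocol article*

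**What the plan says.** Protocol article, 2.9 (Statistical Analysis), names an MMRM for the primary outcome and describes it as "setting each group and visit as a fixed effect and participants as a random effect". No other dependence term and no group-by-visit term is listed; covariates may be added to the fixed effects if necessary.

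The same section carries the primary model over to several secondary outcomes: "CSS scores for 4 weeks against baseline and cough VAS, NDS, LCQ-K, and QCSCS scores will be analyzed using the same methods".

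Three other places bear on the point:

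- Section 2.2.1, inclusion criterion 3, sets lower limits on CSS at entry: "patients with a score above daytime cough symptom score ≥ 2 points and nighttime cough symptom score ≥ 1 point".
- Section 2.4.1 gives each of the two CSS items a range of 0 to 5, so the total runs from 0 to 10, and states "CSS will be assessed at visits 1, 2, 3, and 4". Table 1 places these visits at weeks -2, 0, 2 and 4. The abstract names all four time points when it describes the primary outcome.
- Section 2.2.2 plans for 24 evaluable participants, 12 per group, and recruits 30.

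**The concern.** The label and the description do not match. An MMRM usually means a model in which variances and correlations of the repeated measurements may differ by visit. A participant random effect with ordinary independent residuals allows neither. A programmer working from 2.9 alone would fit the restricted model.

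The design gives reasons to doubt equal variances and correlations for CSS. Visit 1 is truncated by the entry limits. Visit 3 follows two weeks of treatment, and visit 4 follows two weeks off it. If participants respond to different degrees, post-treatment variance rises; if most scores fall towards 0, it shrinks. Correlations may also weaken as visits lie further apart.

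The contrasts at risk are the visit-specific ones: the group difference at week 2 or week 4, and the change from baseline. Section 2.9 names one of them among the secondary outcomes ("Among the secondary outcome measures, CSS scores for 4 weeks against baseline"). Section 4 says that the effect size found here will set the size of the next trial, so the precision attached to these estimates matters even in an exploratory study.

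**Working it through.** **The plan's own figure.** The only related number is the sample size: 24/(1 - 0.20) = 30, or 12/0.80 = 15 per group. It reproduces. The documents state no SD, visit correlation or standard error for CSS, so everything below rests on assumed values.

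**Formulas.** Take complete data, equal arms, a group-by-visit term, and K modelled visits with SDs s1 to sK.

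- Group difference at visit k. The random-intercept model replaces the variance at that visit by the average over visits, so model SE / true SE = sqrt(mean of the s²) / sk.
- Change from visit j to visit k. The model uses 2 × (mean variance - mean covariance); the truth is sj² + sk² - 2 × cov(j,k).

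A ratio below 1 means intervals that are too narrow. A rough large-sample type I error is 2 × [1 - Φ(1.96 × ratio)].

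**Step 1: effect of the entry limits.** Integer day and night scores (0-5 each) were simulated with the entry rule applied at visit 1. Assumptions: latent item SD 0.8-1.2, visit correlation 0.4-0.8 (constant or decaying), day/night correlation 0.5, post-treatment fall 0-1.8 points per item. The SD was 1.15-1.5 at visit 1 and 1.4-1.75 at visit 2. Truncation is real, but mainly at screening.

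**Step 2: group difference, scores barely fall.** One such case has SDs 1.15, 1.56, 1.64, 1.66.

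- Mean variance: (1.3225 + 2.4336 + 2.6896 + 2.7556)/4 = 2.300; square root 1.517.
- Week 2: 1.517/1.64 = 0.925. Week 4: 1.517/1.66 = 0.914. Rough type I error 7.0% and 7.3%.
- With visits 2-4 only: sqrt(7.8788/3) = 1.621; ratios 0.99 and 0.98.

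**Step 3: group difference, scores fall towards the floor.** One such case has SDs 1.33, 1.63, 1.32, 1.32.

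- Mean variance: (1.7689 + 2.6569 + 1.7424 + 1.7424)/4 = 1.978; square root 1.406.
- Weeks 2 and 4: 1.406/1.32 = 1.065. Rough type I error 3.7%. The direction has reversed.

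**Step 4: change from visit 2, correlation decay alone.** Assume equal unit variances and correlations 0.6, 0.36 and 0.216 at one, two and three visits apart.

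- Mean correlation over the six pairs: (3 × 0.6 + 2 × 0.36 + 0.216)/6 = 0.456. Model variance of a change: 2 × (1 - 0.456) = 1.088.
- Change to week 2: true variance 2 × (1 - 0.6) = 0.80; ratio sqrt(1.088/0.80) = 1.17; rough type I error 2.2%.
- Change to week 4: true variance 2 × (1 - 0.36) = 1.28; ratio sqrt(1.088/1.28) = 0.92; rough type I error 7.1%.

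One wrong assumption can thus make one contrast too cautious and another too liberal in the same analysis.

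**Step 5: range over the scenarios of step 1 (model SE / true SE).**

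| Visits modelled | Group difference, week 2 or 4 | Change from visit 2 |
|---|---|---|
| 1-4 | 0.91-1.07 | 0.89-1.15 |
| 2-4 | 0.98-1.10 | 0.86-1.09 |
| 3-4 | 0.99-1.01 | not estimable |

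**Step 6: type I error, integer CSS, 12 per arm, 8,000 null trials per scenario.**

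- Four scenarios with response varying between participants (SD 1.84-2.08 after treatment, 1.5-1.65 before): 6.9-9.0% for the week-2 difference with visits 1-4. For change from visit 2, 4.4-8.0% with visits 1-4 and 4.9-8.2% with visits 2-4.
- Four scenarios with a uniform shift or none: 3.8-5.3% for the week-2 difference, 2.2-5.9% for change.
- A separate run of 6,000 trials with smaller post-treatment SD: about 2-4% for the week-2 and week-4 differences with visits 1-4.
- Unstructured covariance, over all the runs made: 4.4-5.6%.
- Group effect averaged over visits, random intercept: 4.5-5.5% in every case.

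**The case against.** The strongest reply is that 2.9 states no residual covariance. A model with a participant random effect can also carry a structured residual, and an article commonly leaves such detail to the analysis plan. So it is too much to say that the protocol fixes compound symmetry. What remains is that 2.9 is not silent: it names a dependence term, and that term, taken alone, gives compound symmetry.

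A reader might infer that the week-2 and week-4 standard errors are too small. The documents do not support this. They give no CSS variance at any visit, and the sign turns on which visits are responses, how response varies, how correlations decay and how close scores come to 0. Type I errors near 11% needed an assumed pre-treatment SD far below the post-treatment SD at both early visits, whereas the entry rule shrinks mainly visit 1.

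A reader might also infer a higher correlation between visits 1 and 2 because they lie close together. Table 1 spaces all four visits two weeks apart.

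The model as listed has no group-by-visit term. Its single group effect is averaged over visits and keeps its error rate in complete data. That is correct, and it limits the concern to visit-specific contrasts. But a model without that term cannot deliver the group comparison at week 4 against baseline that 2.9 lists.

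Finally, the entry-limit argument does not reach VAS, NDS, LCQ-K or QCSCS. They are measured at visits 2-4 only, and inclusion criterion 3 limits CSS alone.

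**Conclusion.** The point holds in a limited form. Read literally, the stated dependence term imposes equal variances and correlations that the CSS design makes doubtful, and it fits poorly with the MMRM label. Over the assumed scenarios the standard error of a visit-specific contrast ranged from about 14% too small to 15% too large. Type I error was mostly about 6-9% where response was heterogeneous, and about 2-4% where floor effects (for the visit difference) or correlation decay (for the change to week 2) inflated the standard error. If only visits 3 and 4 are responses, the problem almost vanishes.

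These sizes rest on assumed SDs, correlations and response patterns, complete data, 12 per arm and an added group-by-visit term. In an exploratory trial this is a moderate matter. It is worth correcting because the change is cheap and the unstructured model held its level in every scenario tried.

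**What to change.** In 2.9, replace the participant random effect by an unstructured within-participant covariance across the modelled visits, with Kenward-Roger degrees of freedom. Add a group-by-visit term so that the week-2 and week-4 contrasts are estimated. Name one fallback in advance for non-convergence that keeps visit-specific variances, such as heterogeneous Toeplitz. Use the same model for the secondary outcomes that follow the primary method; the reason there is consistency, not the entry limits.

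The cost is one sentence in the plan and a small change in the code. An unstructured matrix has K(K+1)/2 parameters: 6 for three visits and 10 for four, which 24 to 30 participants can support. The downside is those extra parameters and sometimes slightly wider intervals.

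### Covariates for the primary model may be picked by baseline significance tests or by discretion, and baseline CSS is not fixed as one of them

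*Protocol article*

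**What the plan says.** All of this is in section 2.9 of the protocol article unless another section is named.

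- **Primary model.** CSS is analysed by MMRM, "setting each group and visit as a fixed effect and participants as a random effect". No other term is fixed.
- **Covariates.** "If necessary, the fixed effects will include variables with significant differences in demographic characteristics or variables that can affect chronic cough". This opens two routes, both subject to a judgement of need, and neither comes with a list.
- **Baseline tests.** The section first says: "Descriptive statistics for each group regarding demographic characteristics and baseline data will be presented". For continuous variables it adds that "an independent *t*-test or Wilcoxon rank-sum test will be performed depending on their normality", with χ2 or Fisher's exact test for categorical ones. These are the tests that would supply the significant differences.
- **Baseline CSS is collected.** Section 2.4.1: "CSS will be assessed at visits 1, 2, 3, and 4". Table 1 places visits 1 and 2 before treatment.
- **Its role is not stated.** In the efficacy analysis, CSS at baseline appears only in the sentence on secondary outcomes: "CSS scores for 4 weeks against baseline and cough VAS, NDS, LCQ-K, and QCSCS scores will be analyzed using the same methods". Whether it is a covariate, a repeated response or part of a change score is not said.
- **Allocation.** Section 2.7.1: "The participants are allocated according to blocked randomization without stratification". Baseline CSS is therefore not balanced by design.

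**The concern.** In a randomised trial a baseline difference between arms is a chance difference. Testing it does not show whether the variable predicts cough, and prediction is what makes a covariate worth including. The first route can therefore admit an irrelevant variable because of a chance result, and pass over a prognostic one whose imbalance falls short of significance. The second route does aim at prognosis, but with no variable named it lets the analyst settle the primary model after seeing the data.

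Baseline CSS is the obvious candidate. The first route refers to demographic characteristics, so baseline CSS may not be eligible there; it could come in by the second route, but only if someone chooses it.

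At stake are the precision of the primary estimate and its independence from the analyst. Section 4 says the effect size from this trial will be used to size the next one, so a noisy or chosen estimate carries forward.

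**Working it through.** **1. The plan's own figure.** Section 2.2.2 gives 12 per group and 20% dropout: 24/(1 − 0.20) = 30, or 15 per group. This reproduces. The 12 per group follows a recommendation for pilot studies, so there is no power figure to check.

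**2. How often the first route fires by chance.** For k independent tests at 5%, the probability of at least one significant result is 1 − 0.95^k. The article gives neither k nor the test level; both are assumed.
- k = 3: 1 − 0.857 = 0.14
- k = 5: 1 − 0.774 = 0.23
- k = 10: 1 − 0.599 = 0.40

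**3. How large an imbalance must be to count.** The threshold is t(0.975, 2n − 2) × √(2/n) standard deviations.
- n = 12: 2.074 × 0.408 = 0.85 SD
- n = 15: 2.048 × 0.365 = 0.75 SD

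Sizeable imbalances in a prognostic variable can stay below this line.

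**4. What fixed adjustment for baseline CSS gains.** Let r be the correlation of baseline with follow-up CSS (assumed), with equal SDs at both times. Relative to post-treatment scores alone, the variance of the group difference is 1 − r² with baseline as covariate and 2(1 − r) with a change score. Covariate adjustment relative to a change score is (1 − r²)/[2(1 − r)] = (1 + r)/2.

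| r | Covariate vs post-only | Same, simulated, 12 per group | Change score vs post-only | Covariate vs change score |
|---|---|---|---|---|
| 0.3 | 0.91 | 0.94 | 1.40 | 0.65 |
| 0.5 | 0.75 | 0.80 | 1.00 | 0.75 |
| 0.7 | 0.51 | 0.54 | 0.60 | 0.85 |

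The simulation used normal data and 10,000 runs per setting. Its gains are slightly smaller than the large-sample formula gives, since the slope must be estimated from few participants.

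**5. What selection by test would recover.** In the same simulation, baseline CSS was adjusted for only when its own between-group test gave p < 0.05. This is generous to the rule, because CSS may not be a candidate for it.

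| 12 per group | r = 0.3 | r = 0.5 | r = 0.7 |
|---|---|---|---|
| Relative variance, test-based rule | 0.98 | 0.96 | 0.87 |
| Relative variance, always adjusted | 0.94 | 0.80 | 0.54 |
| Power at an assumed 1 SD effect, test-based rule | 0.65 | 0.66 | 0.66 |
| Power at an assumed 1 SD effect, always adjusted | 0.67 | 0.75 | 0.89 |

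**6. Type I error, two-sided 0.05.**
- Overall, test-based rule: 0.037 to 0.049 at 12 per group and 0.035 to 0.049 at 15. There is no inflation.
- Given a moderate baseline imbalance (1.28 to 1.96 standard errors) at 12 per group: about 0.07, 0.09 and 0.12 unadjusted for r = 0.3, 0.5 and 0.7, against about 0.05 to 0.06 with baseline as covariate.

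**The case against.** **Leaving a covariate unnamed is normal in an article; the SAP may name it.** That would answer a complaint of mere silence. It does not answer a selection rule that the article states. The non-naming of baseline CSS matters here because the stated rule is what would decide whether it enters.

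**The rule is not chance alone.** This stands. The second route is prognostic in intent, baseline CSS is admissible through it, and the wording does not force a significant variable in. A reader might infer that baseline CSS is excluded; the text does not say so. The accurate statement is that its inclusion is not fixed.

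**Baseline may already be in the model.** This also stands in part. CSS is measured at all four visits, and the mention of baseline in the secondary analysis hints at change scores. A reader might infer that 24 participants would work like 47 at r = 0.7 (24/0.51). That holds only against an analysis of post-treatment scores alone, which the article does not establish; against a change score the figure is 24/0.85 = 28. Entering pre-treatment CSS as a response is no clean rescue with only the stated main effects. With complete data and equal weights, a group effect δ present only at visits 3 and 4 averages to (0 + 0 + δ + δ)/4 = δ/2 over four visits.

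**The trial is exploratory.** True. No powered hypothesis is stated, and the primary result is reported as a mean with a 95% CI. The main analysis is the FAS of up to 30, so 12 per group is the low end. This limits the severity but does not remove the point.

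**The number of baseline tests is unknown.** Correct. With three tests the figure is 14%, and Fisher's exact test is conservative at this size, which lowers it further.

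**Conclusion.** The concern holds in moderate form and the text should be changed. Section 2.9 lets baseline significance tests, or an open judgement, decide the covariates of the primary model, and it does not fix the baseline value of the primary outcome as one of them.

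A chance trigger would occur in 23% to 40% of trials for an assumed 5 to 10 independent tests at 5%. Prespecified adjustment for baseline CSS would cut the variance by 9% to 49% against post-treatment scores alone (6% to 46% in simulation at 12 per group), or by 35% to 15% against change scores, as r runs from 0.3 to 0.7. The correlation is an assumption throughout. Section 2.2.1 requires minimum cough scores at entry, which narrows the baseline range and may pull r towards the lower values.

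A reader might infer that the rule inflates the false-positive rate. The calculation does not support this for the rule applied mechanically. A free choice among covariates was not simulated, so nothing is claimed about it. What is shown is lost precision, dependence on the analyst, and chance imbalance that may go uncorrected.

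**What to change.** Edit section 2.9 as follows:

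1. Delete the selection of covariates by baseline significance tests and the open-ended second route.
2. Name visit-2 CSS as covariate in the primary model, and state that only visits 3 and 4 are responses, so that pre-treatment CSS is not on both sides of the model.
3. For VAS, NDS, LCQ-K and QCSCS, use each outcome's own visit-2 value in the same way. Table 1 already schedules all four at visit 2.
4. If other prognostic covariates are wanted, name them before unblinding and keep them few. They need not be barred.
5. Describe baseline characteristics by arm, and do not use tests on them to choose the model.

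The cost is a short edit and one degree of freedom in each model. No new data are needed and the recruitment target of 30 does not change.

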## Abstract

Upper airway cough syndrome (UACS) is a common cause of chronic cough characterized by upper airway symptoms, including nasal discharge and throat discomfort. Empirical treatments for UASC-induced chronic cough, such as first-generation antihistamines, have been used; however, the long-term use of these medicines has adverse effects. Therefore, we evaluate the efficacy, safety, and economic feasibility of Wolbigachul-tang (WBGCT), an herbal medication for UASC-induced chronic cough. This is a randomized, double-blind, active-comparator-controlled, parallel, and exploratory clinical trial. Thirty patients with UASC-induced chronic cough will be recruited and randomly allocated to the WBGCT and control groups in a 1:1 allocation ratio. The investigational medicine will be administered three times per day for 2 weeks (3 g of WBGCT at a time). The primary outcome measure is the cough symptom score measured at screening, before starting the trial, and after 2 and 4 weeks. Secondary outcome measures include the cough visual analog scale, nasal discharge score, questionnaire of clinical symptoms of cough and sputum, Leicester cough questionnaire-Korean version, integrative medicine outcome scale, integrative medicine patient satisfaction scale, and 5-level EuroQol 5-dimensional questionnaire, which will be assessed before starting the trial and after 2 and 4 weeks. This study aims to investigate the efficacy, safety, and economic feasibility of WBGCT in the treatment of chronic cough. Therefore, the results of this trial provide evidence for the application of WBGCT in the treatment of UACS-induced chronic cough.

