## 5. Conclusions

This study aims to demonstrate the effects of WBGCT on UACS-induced chronic cough. As WBGCT has been used widely for respiratory diseases over a long period of time with few side effects, WBGCT is expected to be a safe and effective agent for UACS-induced chronic cough. Moreover, considering that our intervention is Korean medicine, we used pattern identification to obtain additional information on whether certain patterns of patients respond better than others to the treatment. Additionally, we perform an economic evaluation of WBGCT compared to SCRT, expecting the expansion of newly applied health insurance-covered herbal formulas. Our study will support the efficacy, safety, and economic feasibility of WBGCT and provide evidence for its clinical use.

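### Week-4 CSS belongs to the primary outcome in the abstract and section 2.4.1 but is secondary in section 2.9, and the stated primary model does not yield the week-2 contrast a reader must infer

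*Protocol article*

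**What the plan says.** All references are to the protocol article.

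- **Abstract, primary outcome:** "The primary outcome measure is the cough symptom score measured at screening, before starting the trial, and after 2 and 4 weeks". Week 4 stands beside week 2 with no difference in rank.
- **Section 2.4.1, primary outcome:** "CSS will be assessed at visits 1, 2, 3, and 4". No decisive visit or change score is named.
- **Section 2.9, week-4 CSS:** "Among the secondary outcome measures, CSS scores for 4 weeks against baseline", to be analysed by the same method as the primary outcome.
- **Secondary lists:** the abstract's list opens "Secondary outcome measures include the cough visual analog scale, nasal discharge score, questionnaire of clinical symptoms of cough and sputum" and goes on to the LCQ-K, IMOS, IMPSS and EQ-5D-5L. Section 2.4.2 covers the same instruments. CSS is in neither.
- **Section 2.9, primary model:** an MMRM, "setting each group and visit as a fixed effect and participants as a random effect", with covariates added if needed. No interaction and no contrast is named.
- **Section 2.9, further CSS analysis:** an RM ANOVA "will be used to compare the differences in the changes in CSS score trends between the groups". Its rank is not stated, and it has its own missing-data rule.

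**The concern.** A reader who follows the abstract and 2.4.1 would count a week-4 difference as part of the primary result. A reader who follows 2.9 would count it as secondary. The two visits answer different questions: treatment lasts two weeks and is followed by two weeks of observation (section 2.1), so week 2 is the effect at the end of treatment and week 4 is persistence after it.

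Two things are at stake. The first is emphasis: whichever visit looks better can be reported as primary with a sentence of the article to support it, and the Conclusions already anticipate that "Our study will support the efficacy, safety, and economic feasibility of WBGCT and provide evidence for its clinical use". The second is planning: the Discussion says that the effect size found here will be used to size the next trial. Week-2, week-4 and visit-averaged effects can differ widely, and the article does not say which one is meant.

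**Working it through.** **1. The plan's own figure.** Section 2.2.2 takes 12 per group and allows 20% dropout: 12 / (1 − 0.20) = 15 per group, 30 in total. This reproduces. It rests on a pilot-study recommendation with no alpha, power, SD or effect size, so there is no power statement to check and it does not show which contrast is primary.

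**2. Passages side by side.**

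| Place | Status of week-4 CSS |
|---|---|
| Abstract, primary outcome | included, no distinction |
| 2.4.1, primary outcome | included, no distinction |
| 2.9 | secondary |
| Abstract, secondary list | absent |
| 2.4.2, secondary list | absent |

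Table 1 has two visits after baseline, week 2 and week 4. If 2.9 makes week 4 secondary, week 2 is left as primary. That is elimination; no sentence says it.

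**3. What the model estimates.** With group and visit as the only fixed effects, the group difference is forced to be the same at every visit in the model, so its estimate is an average over visits. Take an assumed pattern of 0 SD at baseline, 0.8 SD at week 2 and 0.3 SD at week 4:

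- Raw scores at three visits: (0 + 0.8 + 0.3) / 3 = 0.37 SD.
- Change scores at two visits: (0.8 + 0.3) / 2 = 0.55 SD.
- Inferred primary contrast: 0.8 SD at week 2.

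Only a group-by-visit term separates the week-2 difference from the rest.

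**4. Consequence for sizing the next trial.** At equal SD, the required sample size is proportional to 1 / (effect)². In the same assumed pattern, planning on week 4 instead of week 2 multiplies it by (0.8 / 0.3)² = 7.1. This illustrates the leverage of the choice and is not a forecast.

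**5. Chance of a favourable visit under no effect.** Assumptions not in the article: two-sided 5% per test, SD 1 at each visit, equal correlation ρ of 0.3, 0.5 or 0.7 between visits, complete data, and a two-sample t-test on change from baseline standing in for the visit contrast. There were 20,000 simulated trials per setting, with 12 or 15 per group.

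- One named visit: 0.047 to 0.051.
- Week 2 or week 4: 0.088 to 0.093.

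The narrow range is expected. Both changes share the baseline, so their correlation is (1 − ρ) / [2(1 − ρ)] = 0.5 whatever ρ is. Two independent tests would give 1 − 0.95² = 0.0975, and correlation lowers this slightly.

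**The case against.** **Schedule versus hierarchy.** The abstract and 2.4.1 also list screening and baseline, which cannot be efficacy time points, so they read more like measurement schedules than lists of co-primary endpoints. Only 2.9 assigns analysis status, and week 2, the end of treatment, follows from it. This stands in part: the hierarchy is badly worded rather than absent, and a reader who infers that the plan has no primary contrast at all goes too far. But week 2 remains an inference, and the abstract read alone points elsewhere.

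**Condensed article.** Section 2.4.2 describes instruments and need not repeat CSS, and a short account of an MMRM may leave out an interaction that the full protocol contains. This is fair for an omission alone. Here, however, the passages disagree about the rank of week 4, and the listed model terms do not produce the contrast that 2.9 implies.

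**RM ANOVA.** A reader might infer that it could stand in for the MMRM as the primary result. The text does not support that: 2.9 assigns the MMRM to the primary outcome and nowhere makes the RM ANOVA primary. A supportive trend analysis is legitimate, and imputing for it but not for a likelihood-based model is ordinary practice. What remains is only that its supportive role is not written down.

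**Disagreement between visits.** In the simulations with a constant 0.8 SD effect and 12 per group, week-2 and week-4 verdicts differ in about a third of trials (0.30 to 0.34). A reader might take this as the cost of the ambiguity. It mostly reflects low power at this sample size and would be the same after the fix, since both visits would still be analysed. It is not counted here.

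**Exploratory trial.** With no alpha or decision rule, a confirmatory standard does not apply. This stands and limits the conclusion to reporting and planning.

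**Conclusion.** The point holds as an inconsistency within the current text. The abstract and 2.4.1 include week-4 CSS in the primary outcome without distinction, 2.9 ranks it secondary, both secondary lists omit it, and week 2 as primary is only implied. The model as written does not deliver the implied week-2 difference.

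Under the stated assumptions, the open choice between the two visits gives about a 9% chance of at least one significant result with no true effect, against 5% for one named contrast. This assumes that either visit could be presented as primary. The 5% level is itself an assumption, because the article gives only 95% confidence intervals. The figure measures room for selective emphasis and is not an inflated confirmatory error rate. The second consequence is that the effect size to be carried into the next trial is not identified.

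**What to change.** Before unblinding:

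1. State the same primary contrast in the abstract, 2.4.1 and 2.9: the WBGCT minus SCRT difference in change in total CSS from visit 2 to visit 3 (week 2), in the FAS, with its 95% CI. This is the reading most consistent with 2.9.
2. Add a group-by-visit term to the MMRM and take the contrast from it.
3. List week-4 CSS as a secondary outcome in the abstract and in 2.4.2.
4. Label the RM ANOVA on CSS trends as supportive.

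The cost is wording and one extra model term. The sample size stays at 30, with no new visits or data. The small downside is that a difference seen only at week 4, or only in the trend analysis, can no longer be presented as the primary result.
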